#### Interrater reliability

Interrater reliability will be calculated by independent raters for SCID diagnoses before therapy starts (T1) and at the end of therapy, respectively after 26 hours of therapy (T2). We will also calculate interrater reliability for the treatment adherence. The percentage of agreement between the raters on SCID diagnoses, or treatment adherence, will indicate interrater reliability. Based on adequate total observer variance, we will also calculate a more robust measure (e.g. Cohen’s Kappa).

#### Therapist effects

One-way univariate ANOVA on primary outcome measures will show intra-group differences within both treatment conditions at the end of, and 9 and 12 months after the beginning of therapy. As there will be only eight CBT and ST therapists each, resulting in low power, the conclusion that each of them will be equally effective is tentative. Therefore, potential therapist effects will not be examined in this pilot study.

#### Clustering effects

CBT and ST will be administered in two independent centers. There will be considerable interaction among the therapists within each study arm, particularly during training and supervision. Within the ST condition, there will also be interaction between patients, above all in the group therapy session. Due to data dependency, we will conduct two-level (patients, treatment condition) linear regression analysis to account for positive intra-class correlations (ICCs) with respect to the primary outcome measures [91, 92].

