#### Therapists

Recruitment started in 2014, with the first therapists included in September, and was completed in November of the same year. A total of 16 therapists (eight CBT therapists; eight ST therapists) will be involved to conduct two therapies each. CBT therapists will be psychologists in their second to fourth year of training at the CPP. ST therapists will be third- to fourth-year trainees from the Helm Stierlin Institut (HSI), Heidelberg, and the Mannheim Society for Systemic Therapy (MAGST), Mannheim; most of them will be psychologists and educators. Due to the fact that CBT and ST have very different training structures, contents and certification procedures, we chose advanced therapists with different years of training in CBT and ST, respectively, of whom we expected best comparison regarding their training status in theory and practice.

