### Randomization

Following inclusion, patients will be randomized, using block randomization in a 1:1 ratio to obtain equal group sizes [52]. We will use a randomization plan generator (www.randomization.com). An independent research team will conduct the assignment of patients to study arms. Therapists will be randomly assigned to patients as they enter the project.

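### The two-level model meant to handle clustering takes treatment condition as level 2, which leaves two units that are the arms themselves, so no intra-class correlation can be identified

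*Protocol article*

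**What the plan says.** The Clustering effects section of the protocol article gives its reasons for expecting dependent data. Each arm has its own centre ("CBT and ST will be administered in two independent centers"). Therapists influence one another ("There will be considerable interaction among the therapists within each study arm, particularly during training and supervision"). Patients in one arm meet ("Within the ST condition, there will also be interaction between patients, above all in the group therapy session"). Its remedy is this: "we will conduct two-level (patients, treatment condition) linear regression analysis to account for positive intra-class correlations (ICCs", applied to the primary outcome measures.

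The Therapists paragraph under Recruitment gives the actual nesting: "A total of 16 therapists (eight CBT therapists; eight ST therapists) will be involved to conduct two therapies each". The Randomization section adds: "Therapists will be randomly assigned to patients as they enter the project".

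The Therapist effects section opens with "One-way univariate ANOVA on primary outcome measures will show intra-group differences within both treatment conditions" and, after noting low power with eight therapists per arm, closes with "Therefore, potential therapist effects will not be examined in this pilot study".

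The between-arm analyses elsewhere are t-test, Mann–Whitney or chi-square tests (Statistical analyses) and a mixed-design ANOVA whose factors are group and time. Neither names a therapist term.

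**The concern.** A random level in a multilevel model needs several units, so that variation between them can be told apart from the fixed effects. Here the named level has two units, and they coincide with both the arms and the centres. The sentence assures the reader that dependency is accounted for, but the specification cannot deliver that.

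The one grouping in the design with enough units to model is patients within therapists, and it is set aside in text that contradicts itself. An analyst following the article would have to improvise. Three outcomes are possible: a standard error that depends on a software default, an ordinary regression that ignores dependency, or a treatment difference reported as an ICC. The last would be unhelpful in a pilot whose purpose is to supply planning values for a main trial.

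**Working it through.** **Inputs.** 32 patients, 16 per arm (Design and sample size). Two treatment conditions, one centre each (Ethical consideration; Clustering effects). 16 therapists, eight per arm, two patients each (Recruitment, Therapists). Group as a fixed factor (Mixed-design ANOVA). The article gives no ICC, so a therapist ICC of 0.05 to 0.20 is assumed. The article states no figure for this model, so there is none to reproduce. Its sample-size figures (350 for 0.3 SD, pilot of 32) do reproduce and are not in question.

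**Step 1: arm as level 2 and as the fixed contrast.** Between-cluster degrees of freedom = 2 clusters − 2 fixed parameters (intercept, arm) = 0. As a check, the restricted log-likelihood of this model was evaluated on one simulated 32-patient data set with residual variance 1. It was −15.55601 at every arm-level variance tried from 0 to 10. The likelihood is flat, so neither the variance nor the ICC is identified. The standard error of the arm contrast is then whatever the assumed variance makes it:

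SE = √(2σ²_arm + 2/16)

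| Assumed σ²_arm | SE (SD units) |
|---|---|
| 0 | √0.125 = 0.35 |
| 0.1 | √0.325 = 0.57 |
| 1 | √2.125 = 1.46 |

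These values show non-identifiability. They do not estimate any error the trial would make.

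**Step 2: arm as a random effect only.** Two units leave 2 − 1 = 1 df. The variance between two arm means that differ by d is d²/2, so with unit within-arm variance the apparent ICC is (d²/2)/(d²/2 + 1):

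- d = 0.3: 0.045/1.045 = 0.04
- d = 0.5: 0.125/1.125 = 0.11
- d = 0.8: 0.32/1.32 = 0.24

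This is the treatment effect under another name. In simulation the variance was estimated as zero in 67%, 53% and 45% of runs at a true arm-level ICC of 0, 0.05 and 0.10.

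**Step 3: arm as an ordinary covariate.** No cluster unit is then named and no ICC is modelled, so this reading does not rescue the sentence either.

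**Step 4: therapist as level 2, arm fixed.** Degrees of freedom for the arm contrast = 16 − 2 = 14 (two-sided 5% critical value 2.14, against 2.04 on 30 df). Design effect = 1 + (2 − 1) × ICC:

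| Assumed ICC | Design effect | SE ratio | Effective N (32/DE) | Type I error, patient-level t-test ignoring therapist (simulated) |
|---|---|---|---|---|
| 0.05 | 1.05 | 1.02 | 30.5 | 5.6% |
| 0.10 | 1.10 | 1.05 | 29.1 | 6.2% |
| 0.20 | 1.20 | 1.10 | 26.7 | 7.3% |

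A test on therapist means stayed at about 5% throughout. With equal cluster sizes the arm mean difference is the same with or without the therapist term.

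**Step 5: precision of the therapist ICC.** Pooled within arm, the ANOVA has 14 df between and 16 df within therapists. For pairs, ICC = (F − 1)/(F + 1), so an estimate of 0.10 means F = 1.1/0.9 = 1.22. The 97.5% points are 2.82 for F(14,16) and 2.92 for F(16,14). The limits for F are 1.222/2.817 = 0.434 and 1.222 × 2.923 = 3.573. The 95% interval for the ICC therefore runs from −0.566/1.434 = −0.39 to 2.573/4.573 = 0.56.

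**The case against.** The best defence is that little depends on this model. All analyses are declared descriptive and exploratory, and the group comparisons come from the simple tests and the mixed-design ANOVA. In the planned balanced layout the arm difference does not move. Leaving therapist effects out is disclosed and reasoned. No section promises a therapist ICC, and one from 16 pairs would say little: at a true ICC of 0.05 the estimate would be zero or negative in about 43% of trials. A therapist level also does not capture what the Clustering effects section itself names, since shared training and supervision and the ST group session cut across therapists within an arm.

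Most of this stands, and it limits both the size of the point and what the fix can claim. It does not repair the sentence. Disclosing under Therapist effects that therapists are not examined does not make the model under Clustering effects estimable. Low power to show that therapists differ is also a weak reason for leaving them out as a variance component.

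Two stronger inferences should be resisted. A reader might conclude from the table in Step 1 that the trial's standard errors would be wrong several-fold. The documents do not support that, because those values only echo an assumed variance. A reader might also conclude that the pilot fails to deliver a quantity it committed to. Its stated products are effect sizes, a sample size for the main trial, and recruitment and retention.

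**Conclusion.** The point holds as a fault of specification. As written, the level-2 unit is the arm, the level-2 variance and ICC are not identified when arm is the fixed contrast, and the model cannot account for the dependency it is meant to address. The Therapist effects section contradicts itself on whether therapists are analysed.

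The numerical consequence is small: SE about 2% to 10% higher for an assumed therapist ICC of 0.05 to 0.20, with the arm mean difference unchanged. This rests on that assumed range and on the planned two patients per therapist being achieved; unequal clusters after dropout would alter it slightly. In an exploratory pilot this is something that should be fixed, not a defect that invalidates the comparison.

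**What to change.** 1. Under Clustering effects, replace the specification with a two-level model: patients (level 1) within therapists (level 2; 16 therapists, two patients each), treatment as a fixed effect, and about 14 df for the arm contrast. Report the therapist ICC with its confidence interval as descriptive only.
2. Reconcile the Therapist effects section with that model. Either drop the one-way ANOVA or say what its factor is and how it relates to the model, and remove the statement that therapist effects will not be examined. The caution that 16 therapists cannot show equal effectiveness can stay.
3. Add a limitation: dependency from shared training and supervision and from the ST group session, and the complete confounding of arm with centre, cannot be separated from the treatment effect by any model in this design.

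The cost is a few sentences and one respecified model. The drawback is a very imprecise ICC (about −0.39 to 0.56 around an estimate of 0.10), so it should not be used alone as a planning value for the main trial.

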#### Intention-to-treat and per-protocol analyses

The main analyses of all outcomes will be conducted on the intention-to-treat sample, comparing both treatment groups with 32 participants originally allocated after randomization [93]. This calculation will be regardless of whether the patients are detected to violate inclusion criteria, whether they complete therapy or not, or whether they are withdrawn from the study sample due to protocol deviations (e.g. changed use of medication, concurrent psychotherapy during the study period [94]). This will be followed by per-protocol analysis for the primary outcome measures (LSAS, SIAS, SPS) with only patients who fulfill all inclusion criteria, complete the intervention and do not deviate from the protocol.

#### Mixed-design ANOVA

We will perform mixed-design ANOVA to identify differences between treatment conditions [95]. Factors will be group (CBT or ST) and time (baseline, 8th, 15th, 20th therapy hour, end of therapy, respectively 26th therapy hour, 9 and 12 months after the beginning of therapy). Contrasts A will compare baseline with end of therapy. Contrasts B will indicate change between end of therapy, respectively 26th therapy hour, and 9 months after the beginning of therapy. Contrasts C will indicate change between end of therapy and 12 months after the beginning of therapy. We will control for differences in the length of treatment.

Time X Group interaction effect sizes will be assessed with partial eta-squared (η^2^) for the mixed-design ANOVA. Classification of effect sizes will be: η^2^ ≥ 0.01, small effect; η^2^ ≥ 0.06, medium effect; and η^2^ ≥ 0.14, large effect. Subsequently, for significant Time X Group interactions, simple effect analyses within and between groups will be performed [96]. Between-group effect sizes will be assessed with η^2^ and Cohen’s *d*. Classification of Cohen’s *d* will be: *d* ≥0.20, small effect; *d* ≥0.50, medium effect; and *d* ≥0.80, large effect [34]. In accordance with Coe [97], we will interpret Cohen’s *d* in terms of percentiles. Within-group effect sizes will be assessed with η^2^.

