##### Therapy (T1 to T5)

We will assess study outcomes before the start of therapy, after the 8th, 15th and 20th hour of therapy, as well as after therapy has ended. At each time of assessment, patients will participate in an online survey (UNIPARK) including study outcomes (Table 1). The assessment will be conducted at the IMP. Baseline data (T1) will be scheduled no more than 5 days before the first therapy session. Therapy process (T2 to T4) will be assessed no more than 5 days after the 8th, 15th and 20th hour of therapy. The primary endpoint (T5) will be defined by a joint patient-therapist decision to end therapy or by the end of 26 hours of therapy. All outcome variables will be assessed anew, along with in- and outpatient health care service data. A post-SCID and social network interview will also be conducted. Like the pre-SCID, the post-SCID interviews will be rated by independent raters considering primary and secondary diagnoses.

**Table 1 Tab1:** Assessment measures and application plan

Purpose	Perspective	Domain	Instrument	Screening	Baseline	8th, 15th, 20th hour of therapy	End of therapy, no later than 26th hour of therapy	9 and 12 months after beginning of therapy
					T1	T2 to T4	T5	T6 and T7
Screening	Pat	Social anxiety	LSAS-SR	X				
	Diag	Mental disorder SAD	SCID: SAD	X				
Outcome	Diag	Mental disorders	SCID I, II	X			X	
	Pat	Social anxiety	LSAS-SR	X	X	X	X	X
	Pat	Social anxiety	SIAS	X	X	X	X	X
	Pat	Social anxiety	SPS	X	X	X	X	X
	Diag	Global functioning	GAF	X	X		X	
	Pat	Depression	BDI-II	X	X	X	X	X
	Pat, Ref	General symptom severity	BSI	X	X	X	X	X
	Pat, Ref	Experience of social systems	EXIS	X	X	X	X	X
	Pat, Ref	Evaluation of social systems	EVOS	X	X	X	X	X
	Pat, Ref	Dyadic adjustment	DAS-12	X	X	X	X	X
	Pat	Interpersonal problems	IIP-32	X	X	X	X	X
	Pat, Ref	Symptom adjustment	ASS	X	X	X	X	X
	Ref	Burden	BAS		X	X	X	X
Process	Pat, T	Therapeutic alliance	SACiP			X	X	X
	Pat, T	Therapeutic relationship	SRS			X	X	X
	Pat	Therapy motivation	URICA			X	X	X
	Pat, T	Credibility	OAT		X			
Therapists	T	Common therapist factors	DPCCQ		X	X	X	X
Quality	R	Adherence and competence	STAS, CTAS-SP		X	X	X	X
Additional service	Pat	Service receipt	CSSRI-EU				X	X

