### Participation and attrition, responses to crises and suicidality

We will measure participation and attrition by counting the number of interested persons who will 1) contact the recruiting office, 2) participate in the initial screening, 3) will be SCID-interviewed, 4) included into the pilot study, 5) drop out before the beginning of therapy, 6) start therapy, 7) drop out during therapy, 8) end therapy, 9) participate in the 9 months follow-up, and 10) participate in the 12 months follow-up. We will describe causes for withdrawing, and calculate the retention rate for both study conditions separately and together.

Patients will be instructed to contact the therapist and/or research team whenever experiencing adverse events. No constraints will exist regarding additional therapeutic consultations. Inclusion criteria will, however, not allow for use of additional counseling or therapeutic support during the study period.

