### Statistical analyses

All statistics will be descriptive and explorative using the SPSS statistical package (version 19.0; IBM, Frankfurt, Germany). In addition to descriptive measures such as mean, standard deviation, median, interquartile range and confidence intervals, comparisons of primary endpoints between the two groups will be performed using t-test, Mann–Whitney U test and chi-square test, as appropriate. Missing values on less than 20 % of items for each scale of all outcome measures will be replaced with the conditional mean values for the CBT or ST group.

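### The seven-occasion mixed-design ANOVA does not fit the commitment to analyse all 32 randomized patients, and the end-of-therapy assessment is defined inconsistently for patients who leave on their own decision

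*Protocol article*

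**What the plan says.** All places are in the protocol article.

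- **Intention-to-treat and per-protocol analyses:** the main analyses of all outcomes are by intention to treat, "comparing both treatment groups with 32 participants originally allocated after randomization", regardless of "whether they complete therapy or not".
- **Mixed-design ANOVA:** "We will perform mixed-design ANOVA to identify differences between treatment conditions". The factors are group and "time (baseline, 8th, 15th, 20th therapy hour, end of therapy, respectively 26th therapy hour, 9 and 12 months after the beginning of therapy"), seven occasions in all. Contrasts A, B and C use only baseline, end of therapy, 9 months and 12 months.
- **Statistical analyses:** the stated imputation rule has a 20 % ceiling; gaps below that share "of items for each scale of all outcome measures will be replaced with the conditional mean values for the CBT or ST group". The same section plans t-test, Mann-Whitney and chi-square comparisons of the primary endpoints.
- **Therapy (T1 to T5):** T2 to T4 follow the 8th, 15th and 20th hour of therapy. T5 is "defined by a joint patient-therapist decision to end therapy or by the end of 26 hours of therapy". The opening sentence of that section and the T5 column of Table 1 place the assessment at the end of therapy without the joint-decision condition.
- **Participation and attrition:** the patients to be counted include those who "5) drop out before the beginning of therapy" and those who drop out during therapy. No expected rate is given.

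**The concern.** A classical mixed-design ANOVA needs a complete set of values from each patient. Here incomplete sets follow from the design. A patient and therapist who agree to stop before hour 20 produce no T4; before hour 15, no T3 either; before hour 8, none of T2 to T4. Such a patient has deviated from nothing and may have T1, T5, T6 and T7 in full, yet would drop out of the ANOVA, including contrasts that do not use the missing occasions. Dropouts would be lost in the same way, and their 9- and 12-month values with them.

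The pilot exists to supply effect sizes for planning the main trial. If the ANOVA is confined in practice to patients with long, complete therapy, its effect sizes describe that subgroup while carrying an intention-to-treat label. The planned contrast with the per-protocol analysis, which requires completion, would also lose much of its meaning.

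The loss could differ by arm. The Discussion says that CBT tends to use more sessions, and the ANOVA section plans to control for length of treatment.

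**Working it through.** **The plan's own figures.** Design and sample size cites 350 patients for a difference of 0.3 SD (80 % power, two-sided 5 %) and a pilot of 32.

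- Per arm: 2 × (1.960 + 0.842)² / 0.3² = 174.4, rounded up to 175, so 350 in total.
- Pilot, one-sided 80 % limit: 4 × (0.842 / 0.3)² = 31.5, rounded up to 32, which is about 9 % of 350.

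Both reproduce. The 32 contains no allowance for loss.

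**Does another stated rule rescue incomplete patients?**

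- The imputation rule works on items within a scale that was otherwise completed. An assessment that never took place has all its items missing and falls outside the rule.
- The two-level regression under Clustering effects has patients and treatment condition as levels, not occasions within patients. It does not restore missed occasions.
- T6 and T7 run on calendar time and can be collected from dropouts, but a complete-case ANOVA would discard them if T3, T4 or T5 is absent.

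**Size.** The documents give no rate, so the share d of patients missing at least one of the seven occasions is an assumption. Expected number analysed = 32 × (1 − d). Chance that all 32 are analysed, with patients independent = (1 − d)^32.

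| d (assumed) | Patients analysed | Chance of all 32 |
|---|---|---|
| 10 % | 28.8 | 3.4 % |
| 20 % | 25.6 | 0.08 % |
| 30 % | 22.4 | 0.001 % |

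These counts apply to the ANOVA only. I do not turn them into a wider confidence interval for the end-of-therapy difference, because that comparison needs only T5 and has its own, larger number of patients.

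**T5, side by side.** The formal definition has two triggers: joint decision, or 26 hours reached. A patient who stops unilaterally at, say, hour 10 meets neither. The opening sentence of the same section and the Table 1 header would include that patient, since therapy has ended. The intention-to-treat section needs that patient's value. The texts do not agree on whether it is collected.

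**Patients who never start.** Table 1 marks LSAS-SR, SIAS and SPS at screening, so they have a pre-treatment value. T6 and T7 are timed from the beginning of therapy, so these patients have no date for either.

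**The case against.** The strongest reply has four parts.

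1. *Casewise deletion is not stated, and a full protocol or analysis plan may hold a rule for missed assessments.* The first half is true: deletion is a property of the conventional method, and with complete data all 32 would be analysed. But the point does not rest on a missing rule. It rests on a named method with occasions that a compliant patient can lack. A rule elsewhere would have to invent values for therapy hours that never took place.

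2. *The end-of-therapy comparison needs no T2 to T4.* This stands. A reader might infer that the intention-to-treat analysis as a whole cannot be delivered. The documents do not support that: the deletion reaches the ANOVA and its contrasts, not the t-test or Mann-Whitney comparison.

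3. *T5 is not necessarily lost for unilateral leavers.* This also stands. A reader of the formal definition alone might conclude that they never have a T5, but the opening sentence and Table 1 are unconditional. The finding is an inconsistency. Nor do non-starters lack every pre-treatment value, given the screening measures.

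4. *The loss can be made to look too large.* If each of six post-baseline occasions is missed independently with probability 10 %, 32 × 0.9^6 = 17.0 patients remain. That is close to a worst case, because dropout clusters gaps in the same patients: with full clustering the same 10 % leaves 28.8. The 17 should not be used.

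Finally, all analyses are explorative, and the article says that a confirmatory trial must come before any claim of efficacy. That lowers the weight of the point but does not remove it, because effect sizes for planning are what the pilot is for.

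**Conclusion.** The conflict is real and of moderate weight. The ANOVA as specified would in all likelihood analyse fewer than the 32 patients promised: about 29 to 22 if 10 to 30 % of patients miss any occasion. That range is assumed, and the conclusion also rests on conventional casewise deletion. With no missed occasion there would be no loss.

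The effect sizes would lean towards patients with long, complete therapy. Neither the direction nor the size of any bias in the comparison between arms can be derived from the documents. In particular, nothing shows that those who end early are those who remit early. The sample-size figures are correct, and the end-of-therapy t-test or Mann-Whitney comparison is untouched by the seven-occasion deletion. Separately, the T5 wording needs reconciling for patients who leave without a joint decision.

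**What to change.** **Analysis.** Replace the mixed-design ANOVA by a likelihood-based linear mixed model for repeated measures (MIXED in SPSS, the package already named), using all available data from all randomized patients. Estimate contrasts A to C from T1, T5, T6 and T7, and analyse T2 to T4 separately as process data. Four occasions also keep the model manageable at this size: an unstructured covariance has 4 × 5 / 2 = 10 parameters, against 7 × 8 / 2 = 28 for seven. State the missing-at-random assumption.

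**Assessment.** Reconcile the T5 definition with the opening sentence of its section and with Table 1, so that the T5 questionnaires are also collected from patients who stop without a joint decision. Give T5 to T7 a calendar anchor, for example the date of randomization, for patients who never start.

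**Cost.** A change of wording and some follow-up of leavers by online survey. Partial eta-squared is no longer the natural output, so mean differences and Cohen's d (already planned between groups) would be reported instead. The article describes the trial as still recruiting, so the T5 change should come first: values not collected at the time cannot be recovered, whereas the model can be changed at any point before analysis.

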**Design:**

This article describes the rationale and protocol of a prospective, open, interventive, balanced, bi-centric, pilot randomized controlled trial (RCT). A total of 32 patients with a primary SCID diagnosis of social anxiety disorder will be randomized to either CBT or ST. Both treatments will be manualized.

The primary outcome will include social anxiety symptoms at the end of therapy. Therapy will be restricted to no more than 26 hours (primary endpoint). Secondary outcomes will include psychological, social systems and interpersonal functioning, symptom adjustment, and caregiver burden, in addition to change measures, therapist variables and treatment adherence. At the secondary endpoints, 9 and 12 months after the beginning of therapy, we will again assess all outcomes.

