### Efficacy

The efficacy of CBT for social anxiety disorders is well established [31]. A meta-analysis of 29 RCT studies showed a general effect size of 0.70 [32]. The largest German multicenter RCT investigating social anxiety disorders is the Social Phobia Psychotherapy Network (SOPHO-NET; *n* = 495) [18]. The SOPHO-NET was initiated by the lack of evidence for the efficacy of a new psychotherapy method for social anxiety disorders. In the SOPHO-NET, this was psychodynamic therapy (PD) which was compared to CBT. Based on the Liebowitz Social Anxiety Scale (LSAS), the authors investigated remission (LSAS score ≤30) and response (LSAS score reduction of at least 31 %) demonstrably comparable to an improvement of ≤2 in the Clinical Global Impression (CGI) [33]. The authors expected superiority of CBT with a small effect (Cohen’s *h* = 0.30; i.e. CBT response rate of 70 %, PD response rate of 55 %) [34]. With smaller effect than expected, results demonstrated superiority for remission (36 % CBT, 26 % PD; *h* = 0.22) but not for response (60 % CBT, 52 % PD) [35]. Again with small effect sizes, secondary interpersonal outcome measures such as the Inventory of Interpersonal Problems (IIP) [36] also showed significant differences in favor of CBT. At 6, 12 and 24 months after the end of treatment, significant between-group differences were no longer found in any outcome. Contrariwise, some other studies found that CBT patients tend to continue with problems in relationship formation after the end of therapy [37, 38].

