## Hypotheses

The main focus of this paper is to answer the question of what effect sizes of ST can be expected compared to CBT, to calculate how many patients will be needed to replicate effects indicated in this study. For that purpose, we descriptively and exploratively analyze the following hypotheses.**H1: Effects for social anxiety at the end of therapy (primary endpoint).** According to the SOPHO-NET [36] and the study by Willutzki and colleagues [5], we expect both CBT and ST to demonstrate a reduction of social anxiety symptoms, and that CBT will show a major change compared to the new ST.**H2: Effects for secondary outcomes at the end of therapy (primary endpoint).** According to the SOPHO-NET [36], we expect CBT to demonstrate a major change compared to the new ST on psychological functioning, social system and interpersonal functioning, symptom adjustment, and caregiver burden.**H3: Effects 9 and 12 months after the beginning of therapy (secondary and tertiary endpoint).** According to the SOPHO-NET [36] and the study by Knekt and colleagues [4], we expect both CBT and ST to show stable effects on primary and secondary outcomes during the follow-up period.

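### No named contrast targets the CBT–ST difference at 9 or 12 months, and the stated between-arm step runs only after a significant interaction

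*Protocol article*

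**What the plan says.** The abstract (Design) treats the follow-up visits as endpoints: "At the secondary endpoints, 9 and 12 months after the beginning of therapy, we will again assess all outcomes". The only follow-up hypothesis, H3, concerns stability: "we expect both CBT and ST to show stable effects on primary and secondary outcomes during the follow-up period".

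The Mixed-design ANOVA section crosses group with all seven occasions, from baseline (T1) to 12 months (T7), and fixes three contrasts:

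- A: "Contrasts A will compare baseline with end of therapy".
- B: "Contrasts B will indicate change between end of therapy, respectively 26th therapy hour, and 9 months after the beginning of therapy".
- C: "Contrasts C will indicate change between end of therapy and 12 months after the beginning of therapy".

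It then states when the arms are compared further: "Subsequently, for significant Time X Group interactions, simple effect analyses within and between groups will be performed". A later sentence plans eta-squared and Cohen's *d* between groups and names no time points. The opening of Statistical analyses limits the t, Mann–Whitney and chi-square comparisons to primary endpoints, and both Hypotheses and Therapy (T1 to T5) place the primary endpoint at end of therapy. The one-way ANOVA under Therapist effects does reach 9 and 12 months, but it works within each arm.

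**The concern.** The Hypotheses section says the pilot is to show what ST effect sizes can be expected relative to CBT, so that a confirmatory trial can be sized. At the two follow-up endpoints, the relevant quantity is the difference between arms at that time. Contrasts B and C measure something else, namely whether that difference has changed since end of therapy. Contrast A starts from baseline but stops at end of therapy.

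The one explicit step that could compare the arms at 9 or 12 months depends on an omnibus test with low power at this sample size. If the condition fails, the named analyses give no follow-up arm estimate with an interval. If estimates appear only after a significant result, they will tend to be too large, which is a poor basis for a sample size.

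The protocol's own expectations make this likely to matter. H1 expects CBT to be ahead at end of therapy, and H3 expects both arms then to hold steady. If both are right, B and C should each show about nothing while CBT is still ahead.

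**Working it through.** **Inputs from the protocol.** 16 patients per arm and 32 in total; seven occasions T1–T7; contrasts A, B and C as quoted.

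**Assumptions, not in the protocol.** SD of 1 at every occasion, equal correlation ρ between occasions of 0.5 to 0.7, complete data, a 5 % level for the interaction test, and the gap profiles below.

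**1. The protocol's own figures.** It gives no figure for the follow-up comparison. Its sample-size figures do reproduce:

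- Main trial: 2 × ((1.960 + 0.842)/0.3)² = 174.4, so 175 per arm and 350 in total.
- Pilot: 4 × (0.842/0.3)² = 31.5, so 32.

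**2. What each contrast estimates.** Let D(t) be the CBT-minus-ST gap at time t, signed so that positive favours CBT. The group parts are:

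- A = D(T5) − D(T1)
- B = D(T6) − D(T5)
- C = D(T7) − D(T5)
- A + C = D(T7) − D(T1), the baseline-to-12-month comparison, which is not named.

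If D(T5) = D(T6) = D(T7), then B = C = 0 whatever the SD or correlation. In 3,000 simulated trials per scenario, with lasting gaps of 0.3, 0.5 and 0.8 SD, B and C averaged within 0.02 of zero and C was significant in 4–6 % of runs. Contrast A recovered the gap.

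| Assumed gaps, T1 to T7 (SD) | A | C | Gap at T7 |
|---|---|---|---|
| (a) 0, 0.15, 0.30, 0.40, 0.50, 0.50, 0.50 | 0.5 | 0 | 0.5 |
| (b) 0, 0.10, 0.20, 0.25, 0.30, 0.10, 0 | 0.3 | −0.3 | 0 |

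**3. How often the interaction condition is met.** The interaction has 6 and (32 − 2) × 6 = 180 df. The noncentrality is λ = (16/2) × Σ(gap − mean gap)² / (1 − ρ).

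- (a) Sum of squares 0.2336. At ρ = 0.5, 0.6, 0.7, λ = 3.74, 4.67, 6.23 and power = 0.24, 0.30, 0.40.
- (b) Sum of squares 0.0836. At the same ρ, λ = 1.34, 1.67, 2.23 and power = 0.11, 0.12, 0.15.

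The simulation used a gap rising linearly to T5 and then constant. At ρ = 0.5 and 0.7 the condition was met in 11–15 % of runs for 0.3 SD, 26–41 % for 0.5 SD and 62–87 % for 0.8 SD.

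**4. Precision of the missing estimate.** The SE of an arm difference at one occasion is √(2/16) = 0.354 SD.

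- Change contrast (C, or baseline to T7): 0.354 × √(2(1 − ρ)) = 0.35 at ρ = 0.5 and 0.27 at ρ = 0.7.
- Baseline-adjusted difference at T7: 0.354 × √(1 − ρ²) = 0.31 at ρ = 0.5 and 0.25 at ρ = 0.7.

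A baseline-to-follow-up change contrast therefore has the same SE as Contrast C under equal correlation. Only the baseline-adjusted version is tighter.

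**The case against.** The strongest reply is that B and C do what they should. H3 is about stability, and change since end of therapy measures stability directly. H1 and H2 place the arm comparison at end of therapy, which Contrast A covers. This stands: B and C are not the wrong test of H3 and should stay.

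A reader might infer that the follow-up difference is not estimated at all. The text does not support that. The model includes both follow-up visits, and the sentence on between-group Cohen's *d* excludes no time point and can be read as unconditional. Descriptive means and confidence intervals are planned without restriction to end of therapy, and the two-level regression under Clustering effects names no time point either. A + C also gives the baseline-to-12-month comparison by arithmetic, although no interval for that sum is planned.

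A reader might also infer that the planned results would point the wrong way. Read together, A and C tell the right story: in (a) a lead gained and kept, in (b) an early lead that disappeared. The error arises only if C is read alone as an endpoint difference, and the protocol labels it as change.

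Nor does the SOPHO-NET result in the Efficacy section show equal arms at follow-up. It says that "significant between-group differences were no longer found in any outcome", which is absence of significance, at times counted from the end of treatment. This trial counts 9 and 12 months from the start of therapy.

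Finally, this is an exploratory pilot reported in a condensed article, and a separate analysis plan may settle the time points for Cohen's *d*. That lowers the severity. It does not remove the point, because the article itself lists the contrasts and states the significance condition.

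**Conclusion.** The point holds in a limited form. No named, unconditional contrast targets the CBT–ST difference at 9 or 12 months. B and C have expectation zero when an arm gap persists unchanged, which follows from their definition and needs no assumption about variance or correlation. The explicit between-arm step depends on an interaction test that would often fail for small to medium effects: it would succeed in about 24–40 % of trials for a lasting 0.5 SD gap and 11–15 % for a 0.3 SD gap that closes. Those percentages rest on the assumed profiles, equal correlation of 0.5–0.7, complete data and 16 per arm. A lasting gap of 0.8 SD would usually pass.

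The significance condition sits badly with a plan that calls itself descriptive and explorative and exists to supply effect sizes. The weight is modest, since the primary comparison is at end of therapy and no confirmatory claim is made.

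**What to change.** For each outcome measured at T6 and T7, state that the between-arm difference at 9 months and at 12 months will be reported with a 95 % confidence interval and Cohen's *d*, regardless of the omnibus interaction. A baseline-adjusted difference is preferable (SE about 0.25–0.31 SD); a baseline-to-follow-up group contrast is an acceptable alternative (SE about 0.27–0.35 SD). Keep contrasts B and C, label them as maintenance contrasts, and say that they do not measure which arm is better at follow-up.

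The cost is a few lines of wording and two more exploratory estimates per outcome, from data already scheduled for collection. The intervals will be wide: with a normal quantile, the baseline-adjusted half-width is about 1.96 × 0.25 = 0.49 to 1.96 × 0.31 = 0.61 SD. They should be presented as planning information, not as evidence of equivalence or superiority.
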